### Evaluating changes in sleep patterns

Participants are instructed to fill in a sleep diary for the last 7 days, documenting sleep timing, duration, waking up during the night, sleep quality, and daytime sleepiness on a continuous basis. This diary allows participants to self-report their sleep experiences, offering an informed view of their sleep patterns over the average of the last week also including any change in sleep-timing that would indicate a circadian effect of treatment.

In addition to the sleep diary, we employ the Pittsburgh Sleep Quality Index (PSQI) at baseline and day 42 of the study. The PSQI is a standardized measure that evaluates seven components of sleep quality, including subjective sleep quality, sleep latency, sleep duration, habitual sleep efficiency, sleep disturbances, use of sleeping medication, and daytime dysfunction.

### Adherence evaluation

Adherence to the device and treatment will be evaluated based on recorded statistics on device usage (in minutes per session). The eye-tracking system within the device will be utilized to quantify the active presence of the participant and gaze direction during each session. Adherence is considered high when the participant is present in front of the device for over 70% of the recommended session time (one hour).

### Exploratory analysis of electroencephalography data

Depression has been associated with various alterations in electroencephalographic (EEG) patterns. In terms of treatment, effective antidepressant therapies, including pharmacological interventions, psychotherapy, and neuromodulation techniques, are shown to cause EEG changes over time and in relation to recovery of faster gamma frequency oscillations [49]. The study will examine two different EEG conditions: resting state activity and SSVEPs responses to 40 Hz strobe light. EEG measurements will be collected at baseline and 6 weeks post-treatment visits to assess the effects of 40 Hz vs continuous light to the resting state activity and evoked responses of depressed patients. No hypothesis testing will be done regarding EEG measurements.

### Data collection

Identifiable data such as full name, address, and social security number will only be shared with key personnel and only for data collection from the electronic patient journal. All data sharing will be according to the European General Data Protection Regulation (GDPPR) and in agreement with permission from the Danish data protection agency. The REDCap system is used for collecting data during patient visits. The only data collected outside of the investigational site is the average usage time of the device, which is stored locally on the device and does not include any personal information. Depression severity measures (HAM-D_17_) will also be collected from the patients that dropped out.

Data collected: Age, gender, social security number, e-mail, phone number, inclusion date, diagnosis, sociodemographic data (residential status, work situation, somatic condition, prior and current depressive episode, smoking, eliciting factors for depressive episodes, suicidality history, alcohol, drug abuse), medical history, depression, mania, quality of life, sleep, side-effect, and suicidality ratings, treatment expectancy, blinding and treatment evaluation, concomitant medication.

### Statistical analysis plan

The analysis will be carried out using R software version 4.2.1 or higher (Free Software Foundation’s GNU General Public License). With a minimal clinically important difference of 3 points on the HAM-D_6_ scale, an expected standard deviation of 3.5, an alpha value of 0.05, and a power of 90%, and considering dropout, we will need a total of 60 patients to show the significance of the primary outcome. Based on the previous studies at Psychiatric Centre Copenhagen, dropout is expected to be below 25%, and we will attempt to administer the HAM-D_6_ (primary endpoint) for all the patients who drop out of the trial. An intention-to-treat population, including all randomized participants, will be used for analyses. The mean change from baseline to post-treatment at day 42 in HAM-D_6_ scores will be compared between treatment groups using a two-sample *t*-test. *T*-test assumptions of normality and equal variance will be checked. A mixed model repeated measures method will be used to analyze depression symptoms from baseline to measurements at day 7, day 21, day 42, and day 56. The Benjamini-Hochberg correction will be used for multiple comparisons. A *p*-value of less than 0.05 is considered a rejection of identity between groups.

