## Study design and interventions

The study is a randomized, double-blinded, placebo-controlled, single-center clinical trial investigating the effects of 40 Hz brain stimulation. Patients are randomly assigned to one of two groups: 40 Hz masked flickering white light (active) and continuous non-flickering white light matched in color temperature and brightness (placebo). This is a double-blind study, so neither the participant nor the researcher will know which treatment the participant is receiving. Both kinds of light appear as white light, so the normal white light serves as a well-matched placebo. As a precaution, the investigators doing the assessments will not see the devices turned on but will instruct the trial participants on correct device use during the baseline meeting. Each participant is handed out a user manual with detailed instructions on how to handle the light therapy and recommended daily usage times. Participants will receive in-person instructions and will be additionally contacted *via* phone to ensure a smooth process and proper implementation of the light therapy.

Participants take light therapy at home; however, the variability in the specific implementation details of the treatment, particularly among subjects with poor adherence, poses potential challenges to the trial’s overall outcome. To mitigate these concerns and enhance the integrity of the study, adherence to the treatment protocol in both groups is monitored using an eye-tracking system. This system documents each participant’s active usage time, ensuring a comprehensive assessment of treatment adherence.

A treatment blinding test will be administered to the participants at day 42. The treatment blinding test assesses the participant’s awareness of which treatment group, he/she was allocated to for assessment of blinding efficacy. In addition, an evaluation of participants’ expectations regarding the effectiveness of the treatment will be systematically conducted at the initial visit, serving as a baseline measure.

An independent investigator will program 30 active treatment and 30 placebo devices in total assigned with labels A and B to the device identification numbers. The statistician creates unequal randomization blocks (e.g. ABBA, BAABBA) where he assigns a patient number (e.g. FELIX01, FELIX02) to the treatment group (A or B) and then the treatment group to a random device (corresponding to the group). The block size is blinded to investigators.

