## Study assessments and endpoints

Study assessments include questionnaires pertaining to the symptoms of depression, and include the assessment of depression severity, suicidal ideation, cognition, sleep duration and quality, general quality of life and mania. Summary of study evaluations and endpoints can be found in (Table 3).

**Table 3. t0003:** Summary of study endpoints.

	Endpoints	Description
Primary	Hamilton Depression Rating Scale 6 (HAM-D_6_) Time points of measurement: baseline, day 7, day 21, day 42, and day 56. The primary endpoint is the mean difference in scores between treatments at baseline and day 42.	The scale is designed to rate the severity of depression in patients by a healthcare professional. The assessment scale contains 6 items pertaining to the symptoms of depression experienced over the last three days. The score ranges from 0 to 24 [0–4] = no depression [5–6] = subclinical depression [7–8] = mild depression [9–11] = moderate depression [12–22] = moderate-severe depression A 2–3-point change in score is considered a minimum clinically important difference (MID) [39,50].
Secondary	Major Depression Inventory (MDI) Time points of measurement: baseline, day 7, day 21, day 42, and day 56	MDI is a depression self-assessment questionnaire. It consists of the 10 ICD-10 symptoms of depression. The sum of 10 questions indicates the degree of depression. The score ranges from 0 to 50 <21 = normal [21 − 25] = mild depression [26–30] = moderate depression ≥ 31 = severe depression [41]
	Neurocognitive battery Time points of measurement: baseline, day 7, and day 42	Assessing attention and recognition of emotional facial expressions using Facial Expression Recognition Test (FERT) and self-referent memory for emotional words using the Emotional Categorization and Memory test (ECMT). Non-emotional cognition is investigated with the Screen for Cognitive Impairment in Psychiatry (SCIP) and the Trail Making Test B (TMT-B) [51,52].
	Sleep diary covering last 7 days. Time points of measurement: continuous, by subjects themselves	Average last 7 days’ sleep parameters: Duration, falling asleep and waking up times, sleep quality, daytime sleep.
	Pittsburg Sleep Quality Index (PSQI) Time points of measurement: Baseline, and day 42	Seven component scores are derived, each scored 0 (no difficulty) to 3 (severe difficulty). The component scores are summed to produce a global score (range 0–21). Higher scores indicate worse sleep quality [53].

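### The 60 patients said to give 90% power after dropout are the number needed with complete day-42 data, so the figure contains essentially no dropout allowance

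*Protocol article*

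**What the plan says.** The sample size is set in the protocol article, section Statistical analysis plan. The target is given as "With a minimal clinically important difference of 3 points on the HAM-D_6_ scale", with "an expected standard deviation of 3.5" and "an alpha value of 0.05, and a power of 90" per cent. The same sentence ends: "and considering dropout, we will need a total of 60 patients to show the significance of the primary outcome". The next sentence says that "dropout is expected to be below 25" per cent, on the basis of earlier studies at the centre, and adds that the team will try to administer the HAM-D6 to everyone who drops out. The analysis population is all randomised participants, and the primary test is a two-sample t-test on change from baseline to day 42.

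Two other places bear on the point. The section Study design and interventions fixes the allocation: "An independent investigator will program 30 active treatment and 30 placebo devices in total". The section Data collection says that the HAM-D17, which contains the HAM-D6 items, will also be obtained from patients who dropped out. It names no time point for that assessment.

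**The concern.** The sentence presents 60 as a figure that already absorbs dropout. A reader will therefore expect the number needed for analysis to be smaller than 60, with the remainder held as a margin for losses. If 60 is itself the number needed for analysis, there is no margin, and each day-42 value that is missing takes power below the stated 90%.

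The 90% is the figure against which a non-significant result will be judged. If a material share of day-42 values is missing, such a result would be read as coming from a better-powered trial than was actually run.

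**Working it through.** **Inputs.** All are from the Statistical analysis plan section unless noted.
- Difference δ = 3; SD σ = 3.5; alpha 0.05; power 90%.
- Allocation 30:30 (Study design and interventions).
- Dropout below 25%, used here as an upper bound.
- Assumption 1: alpha is two-sided. This is not stated, but the decision rule ("A *p*-value of less than 0.05 is considered a rejection of identity between groups") reads that way.
- Assumption 2: 3.5 is the SD of the change score, the variable being tested. The text does not say which SD it is.

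**Step 1. Reproduce 60.**

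Normal approximation: n per arm = 2(z₀.₉₇₅ + z₀.₉₀)²σ²/δ² = 2 × (1.960 + 1.282)² × 12.25 / 9 = 28.6. This rounds up to 29 per arm, 58 in total.

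t-test (noncentral t): noncentrality = δ / [σ√(1/n₁ + 1/n₂)], with n₁ + n₂ − 2 degrees of freedom.
- 29 per arm: 3/0.919 = 3.264, 56 df, power 89.4%.
- 30 per arm: 3/0.904 = 3.320, 58 df, power 90.4%.

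The smallest equal-arm design reaching 90% is therefore 30 per arm, 60 in total. The stated figure is reproduced exactly, before any dropout allowance. On the normal approximation, 60 − 58 = 2 patients are left over, about 3%.

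**Step 2. What an allowance for 25% would give.** 60/(1 − 0.25) = 80 with the t-test, or 58/(1 − 0.25) = 77.3, rounded up to 78, with the normal approximation. The shortcut of multiplying by 1.25 gives 75 or 73. None of these is 60.

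**Step 3. Power as day-42 values go missing from 60 randomised.** The full 3-point effect is assumed in everyone measured.

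| Day-42 values missing | Evaluable | Noncentrality | Power |
|---|---|---|---|
| 0% | 30/30 | 3.320 | 90.4% |
| 10% | 27/27 | 3.149 | 87.1% |
| 20% | 24/24 | 2.969 | 82.8% |
| 25% | 23/22 | 2.874 | 80.2% |

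**Step 4. Effect of retrieval.** Dropout of 25% is 15 patients. If about half are measured at day 42 (8 missing, 26/26), power is 85.8%. If about three quarters are measured (4 missing, 28/28), it is 88.3%. If all are measured, it is 90.4%. The same assumption of a full effect applies.

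**Step 5. Could other inputs explain 60 after dropout?** Each route changes something that the text states or implies.
- One-sided alpha 0.05, normal approximation: 48 evaluable, and 48/0.80 = 60 or 48 × 1.25 = 60. Proper inflation for 25% gives 48/0.75 = 64, and the one-sided t-test gives 50/0.75 = 66.7, or 67.
- Power 80% instead of 90%: 44/0.75 = 58.7, or 59 (normal approximation), and 46/0.75 = 61.3, or 62 (t-test).

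**The case against.** The best defence is that dropout from treatment is not the same as a missing outcome. The plan intends to measure the HAM-D6 in patients who leave, repeats an intention to collect depression ratings from them under Data collection, and analyses everyone randomised. On that view few day-42 values need be missing, and the 90% could largely survive. This stands in part. It means that 80% is a lower bound under two conditions, not the expected power. It does not rescue the sentence: the plan commits only to an attempt, gives no day-42 timing for the retrieved assessment, and adds no patients to cover a failed one.

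A second defence is that a one-sided test was meant. Nothing says so, the decision rule points the other way, and 60 still falls short at 25% with ordinary inflation.

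A third is that the SD is not tied to the change score. That is correct. If 3.5 is the SD of a single score, with equal variances at both visits, the change-score SD is 3.5√[2(1 − r)]: 4.1 at r = 0.3, 3.5 at r = 0.5 and 2.7 at r = 0.7, where r is an assumed baseline-to-day-42 correlation. Power could then be lower or higher than shown. This uncertainty applies to the whole calculation and is not evidence that dropout was allowed for.

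The Discussion concedes that a larger sample might be needed. That is a general caution and does not correct the stated calculation.

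**Conclusion.** The point holds. On the plan's own figures, 60 is the number required with every day-42 HAM-D6 observed, and the claim that it takes dropout into account is not borne out. Power runs from 90% with complete data to about 80% with 25% missing. This rests on a two-sided alpha, 3.5 as the SD of change, and the full 3-point effect in everyone measured.

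Three stronger readings might be inferred, and the documents do not support them.
- That the trial simply has 80% power. This needs dropout at its stated upper bound and no retrieval at all. With complete outcome data the design does have 90%.
- That the 3-point target contradicts the endpoint table in Study assessments and endpoints, which says "A 2–3-point change in score is considered a minimum clinically important difference (MID"). Three points lies inside that range, and powering on its upper end is a design choice.
- That measured dropouts would dilute the effect and lower power further. This is possible, but the documents give no figure for the effect in such patients.

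This should be fixed. It is a misstatement of power, and it does not make the design unusable.

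**What to change.** In the Statistical analysis plan section, replace the sample-size conclusion with wording such as: *60 randomised patients give 90% power for a 3-point difference if all 60 provide a day-42 HAM-D6; if dropout reaches 25% and none of those patients is measured (45 evaluable), power is about 80%.*

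Either delete the phrase about dropout or state the evaluable number and the dropout rate that were used. In the same sentence, say that alpha is two-sided and which SD the 3.5 is. If the sponsor confirms a different sidedness or SD, the two power figures should be recomputed before they are inserted.

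The cost is a change of text only. The number randomised, the devices, the visits and the primary test stay as they are. The stated power becomes less favourable when outcome data are incomplete.

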**Figure 1. F0001:**
[figure not shown]
Visual representation of study design and follow-up visits. HAM-D_17_: Hamilton Depression Rating Scale 17 item version; MDI: Major Depression Inventory; WHO-5 World Health Organization Quality of Life Index; PSQI: Pittsburg Sleep Quality Index; SIDAS: Suicidal Ideation Assessment Scale; YMRS: Young Mania Rating Scale; UKU: The UKU Side Effect Rating Scale; SCIP: The Screen for Cognitive Impairment in Psychiatry. TMT-B: Trail Making Test Part B; FERT-Facial Emotion Recognition Task; ECMT: Emotional Categorization and Memory Test; SSVEPs: Steady State Visually Evoked Potentials.

Patients are free to withdraw from the trial at any time. Drop out criteria include hospitalisation due to a somatic illness, admission to a psychiatric ward for any length of time, side effects at a level unacceptable to the subject, worsening of depression such that it would be unethical not to try other treatments, the patient or the patient’s healthcare provider changes the dose of medication affecting the depression, onset of mania assessed according to the YMRS with a score of 7 or above or fulfilling the diagnostic DSM-5 criteria for a current hypomanic or manic episode, and patients reports conditions treatment that interfere with blinding. Patients who drop out from the trial continue their treatment and follow-up care at Psychiatric Centre Copenhagen.

A GCP monitor (GCP-Unit, University of Copenhagen, Frederiksberg Hospital) has been assigned to the study and will follow the clinical trial, randomization, blinding, and data collection procedures.

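### The primary t-test on day-42 HAM-D6 change covers all randomised patients only if every drop-out is rated at day 42; the mixed model already planned should be the primary analysis

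*Protocol article*

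**What the plan says.** The Statistical analysis plan section states that "An intention-to-treat population, including all randomized participants, will be used for analyses". It assigns the primary endpoint, mean HAM-D6 change from baseline to day 42, to a two-sample t-test. It expects dropout below 25% and adds that "we will attempt to administer the HAM-D_6_ (primary endpoint) for all the patients who drop out of the trial". The Data collection section says that HAM-D17, which contains the HAM-D6 items, will also be collected from drop-outs. Neither section says when these ratings are made.

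A second method follows: "A mixed model repeated measures method will be used to analyze depression symptoms from baseline to measurements at day 7", and then at days 21, 42 and 56. It is not tied to the primary endpoint. The article does not call it secondary; its rank follows from the t-test having been given the primary comparison.

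The drop-out criteria, listed under Figure 1 in Study design and interventions, include "worsening of depression such that it would be unethical not to try other treatments", psychiatric admission and a change in the dose of medication that affects the depression. Table 3 schedules HAM-D6 at baseline and days 7, 21, 42 and 56.

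**The concern.** A t-test on change needs both the baseline and the day-42 score. The promise to analyse everyone randomised is therefore kept only if each patient, drop-outs included, is rated at day 42. The text promises an attempt and gives no time point. Where the attempt fails, the patient leaves the analysis. Where it succeeds before day 42, an earlier score would have to stand in for day 42.

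Several drop-out criteria depend on how the depression is going, so completers are a selected group, and more strongly selected in whichever arm does worse. The day-7 and day-21 scores carry information about that selection, and the t-test discards them. It also handles baseline only by subtraction, not as a covariate. The planned mixed model uses all of these scores but does not produce the headline result.

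At stake are the size of the primary estimate and the power of the trial's main comparison.

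**Working it through.** **Inputs from the Statistical analysis plan section.** "With a minimal clinically important difference of 3 points on the HAM-D_6_ scale"; "an expected standard deviation of 3.5"; "an alpha value of 0.05"; power 90%; 60 patients; dropout below 25%. Allocation is 30 and 30 (Study design and interventions). Sidedness is not stated. I take two-sided, because the criterion "is considered a rejection of identity between groups".

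**The plan's own figure.** The normal approximation gives n per arm = 2 × 3.5² × (1.960 + 1.282)² / 3² = 28.6, so 29 per arm and 58 in total. The exact t-test gives 29.6, so 30 per arm and 60 in total. Sixty is thus what is needed with every patient scored at day 42.

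**Power by number scored at day 42** (difference 3, SD 3.5, exact t-test):
- 60 scored: 90.4%
- 48 scored (20% missing): 82.8%
- 45 scored (25% missing): 80.2%

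These losses come from numbers alone, with no selection.

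**Selection among completers.** The article gives no within-patient correlations and no dropout pattern, so what follows is assumed. The true day-42 difference is 3. The SD of change is 3.5 at days 21 and 42. The two changes correlate at r = 0.3 or 0.5. The day-21 difference is 1 to 2 points. Overall, 15% or 25% drop out, namely those with the worst day-21 change, and none of them is rated at day 42.

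Let z be the cut-off in SD units from an arm's mean day-21 change, and h(z) = φ(z)/Φ(z). Then:

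completer difference = 3 − r × 3.5 × [h(z placebo) − h(z active)]

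Take r = 0.5, a day-21 difference of 1.5 and 25% dropout:
- z is 0.476 on placebo and 0.904 on active, so dropout is 31.7% and 18.3%, mean 25.0%.
- h is 0.522 and 0.324.
- Completer difference = 3 − 0.5 × 3.5 × (0.522 − 0.324) = 2.65.
- Completer variance in an arm is 3.5² × [1 − r² × h(h + z)], which gives a pooled SD of 3.29.
- Power with about 45 completers is about 75%.

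Over the whole grid:

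| r | Completer difference |
|---|---|
| 0.3 | 2.73 to 2.89 |
| 0.5 | 2.54 to 2.82 |

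With probabilistic instead of strict cut-off dropout, simulation gave 2.62 to 2.91. At r = 0.7 the lowest value is about 2.4.

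**The likelihood model.** Selection on the day-21 score does not change the regression of the day-42 score on it. A model that includes day 21 therefore recovers the full difference: 2.98 to 3.01 in simulation. In the 25% dropout scenario with a day-21 difference of 1.5, its power (day 21 only; day 7 and baseline not used) was about 78% at r = 0.3 and about 80 to 81% at r = 0.5. The completer t-test had about 74 to 75% in the same runs.

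**No true effect.** With equal dropout in the two arms, neither method was biased, and the completer t-test kept its error rate at 5.0 to 5.5%.

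**The case against.** The strongest reply is that the article already plans to rate drop-outs. If those ratings are made at day 42, the t-test covers all randomised patients and is a genuine intention-to-treat analysis. That reading is open and it is the favourable one. But the text speaks of an attempt and does not promise a day-42 rating.

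Four stronger readings are tempting and are not supported:
- A reader might infer that drop-outs are rated at withdrawal, so that the primary analysis amounts to last observation carried forward. Nothing in the article says so. Estimates built on that reading also need an assumed mean course over time, and I do not rely on them.
- A reader might infer that a quarter of the day-42 scores will be missing. The 25% is an upper bound on dropout, not a rate of missing scores; each drop-out rated at day 42 lowers the latter.
- A reader might blame the t-test for the whole fall from 90% to 75%. About 10 of those 15 points come from lost numbers. The model recovers roughly 3 to 7 points. The absence of a dropout reserve in 60 is a separate matter.
- A reader might treat the lack of an imputation rule as the fault. Such detail commonly sits in the full protocol or analysis plan, neither of which is shown.

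It is also fair to say that a t-test with a supporting mixed model is a recognised design, that there is no doubt which of the two is primary here, and that some drop-out criteria (somatic admission, side effects, loss of blinding) need not track HAM-D6. These points lower the severity. They do not reconcile the fixed test with the promise to analyse everyone.

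**Conclusion.** The point holds as a should-fix. The stated population and the fixed primary test agree only if every drop-out is rated at day 42, which the article does not promise. Otherwise the primary result leaves out randomised patients or uses an earlier score in place of day 42, while a better-suited method sits unused for the headline comparison.

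The bias is about 0.1 to 0.5 points out of 3, toward the null. That range assumes correlations of 0.3 to 0.5, dropout driven by poor day-21 response, 15% to 25% dropout and no day-42 ratings of drop-outs. It shrinks as more drop-outs are rated at day 42. The power of about 80% with 45 scored needs only the plan's own inputs and a two-sided test; the further drop to about 75% needs the selection assumptions as well. No inflation of the false-positive rate was found when dropout was equal in the two arms.

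**What to change.** Name one primary analysis: the treatment contrast at day 42 from the planned mixed model for repeated measures. Fit it to all randomised patients, with baseline HAM-D6 as covariate, visit, treatment, treatment by visit and an unstructured covariance. Keep the t-test on observed day-42 data as a sensitivity analysis. State when drop-outs are rated, and enter each rating at the time it was actually taken.

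The cost is a change of wording before unblinding, with no new visits or patients. The downside is that the model is unbiased only if dropout depends on observed scores (missing at random). One delta-adjusted sensitivity analysis, which makes the unobserved day-42 scores progressively worse, would check this. The change will not restore 90% power if many day-42 scores are missing.

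### The primary HAM-D6 comparison is a t-test on change that does not adjust for the baseline score; the test is valid, but adjustment would cost one degree of freedom and could gain precision

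*Protocol article*

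**What the plan says.** The section on the statistical analysis plan in the protocol article states the primary comparison: "The mean change from baseline to post-treatment at day 42 in HAM-D_6_ scores will be compared between treatment groups using a two-sample" t-test. It adds that the test's "assumptions of normality and equal variance will be checked". It names no covariate.

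Table 3, under study assessments and endpoints, lists HAM-D6 as the primary measure and gives its schedule: "Time points of measurement: baseline, day 7, day 21, day 42, and day 56". The baseline value is therefore planned for every patient.

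The sample size rests on these inputs: "With a minimal clinically important difference of 3 points on the HAM-D_6_ scale", "an expected standard deviation of 3.5", "an alpha value of 0.05", 90% power and 60 patients in total. The text does not say whether 3.5 is the SD of the change or of the score.

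A mixed model for repeated measures is also planned for depression symptoms over all visits. It is listed separately, is not called primary, and no baseline covariate is stated for it.

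**The concern.** Subtracting the baseline is one way of using it, but it imposes a slope of exactly 1 of day-42 score on baseline score. If the true slope b is below 1, the change score over-corrects. This has two consequences, which are two views of one effect:

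- Averaged over randomisations, the change-score estimate has a larger variance than an estimate that fits the slope.
- In the one randomisation that is carried out, a baseline difference D between the arms moves the change-score estimate by (b − 1) × D. ANCOVA removes that shift.

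At stake is precision in a trial of 60 patients. The planned power of 90% is reached only if all 60 are analysed. The choice of primary test is written into the article, so it is not a detail left to an unseen analysis plan.

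**Working it through.** **Inputs from the documents.** Difference 3 points, SD 3.5, alpha 0.05, power 90%, 30 devices per arm, dropout expected below 25%. Sidedness is not stated. I take the test as two-sided because the decision rule says that a small p-value "is considered a rejection of identity between groups".

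**Assumed inputs, not in the documents.** The correlation r between baseline and day-42 HAM-D6 (0.3 to 0.7), and the ratio k = baseline SD / day-42 SD (1 or 0.7). In the main calculation 3.5 is taken as the SD of change.

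**Step 1: the plan's own figure.** The noncentrality is 3 / (3.5 × √(2/30)) = 3.32 with 58 degrees of freedom, which gives 90.4% power with 30 per arm. The figure of 60 thus reproduces as the number analysed. With 45 analysed (60 × 0.75, split 23 and 22) the t-test has 80.2% power.

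**Step 2: variance ratio.** With the day-42 SD as the unit:

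- variance of change = 1 + k² − 2kr
- residual variance after ANCOVA = 1 − r²
- ratio = (1 − r²) / (1 + k² − 2kr), which is (1 + r)/2 when k = 1
- slope b = r/k

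**Step 3: power.** The ANCOVA residual SD is 3.5 × √ratio, and power is by noncentral t with one degree of freedom fewer.

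| k | r | b | Variance ratio | Residual SD | Power, 60 analysed | Power, 45 analysed |
|---|---|---|---|---|---|---|
| t-test on change | – | – | 1 | 3.50 | 90.4% | 80.2% |
| 1 | 0.3 | 0.30 | 0.65 | 2.82 | 98.2% | 93.6% |
| 1 | 0.5 | 0.50 | 0.75 | 3.03 | 96.5% | 90.0% |
| 1 | 0.7 | 0.70 | 0.85 | 3.23 | 94.3% | 86.1% |
| 0.7 | 0.3 | 0.43 | 0.850 | 3.23 | 94.3% | 86.1% |
| 0.7 | 0.5 | 0.71 | 0.949 | 3.41 | 91.8% | 82.2% |
| 0.7 | 0.7 | 1.00 | 1.000 | 3.50 | 90.4% | 80.2% |

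In the last row b = 1. The change score is then already the right adjustment, and ANCOVA gains nothing.

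**Step 4: if 3.5 is the SD of the score instead** (k = 1). The SD of change is 3.5 × √(2(1 − r)) and the ANCOVA residual SD is 3.5 × √(1 − r²).

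| r | t-test, 60 | ANCOVA, 60 | t-test, 45 | ANCOVA, 45 |
|---|---|---|---|---|
| 0.3 | 78.8% | 92.8% | 66.1% | 83.7% |
| 0.5 | 90.4% | 96.5% | 80.2% | 90.0% |
| 0.7 | 98.8% | 99.5% | 95.2% | 97.6% |

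The variance ratios are those of step 2. The absolute power figures change, and power now rises with r.

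**Step 5: size of the shift from imbalance.** With 30 per arm and an assumed baseline SD of 2.5 to 3.5, the chance baseline difference has a standard error of 2.5 × √(2/30) = 0.65 to 3.5 × √(2/30) = 0.90 points. At an assumed b = 0.5, a difference of 1 point moves the change-score estimate by (0.5 − 1) × 1 = −0.5 point, against a target of 3.

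**The case against.** The strongest reply is that nothing is invalid here. A pre-specified t-test on change is unbiased over randomisation, and its standard error already contains the variation due to chance imbalance. The gain from ANCOVA depends on two quantities that the article does not give, and it vanishes when b is near 1. The planned mixed model could also supply a baseline-adjusted day-42 contrast. All of this stands, and it limits the point to efficiency. It does not remove the point, because the mixed model is not the primary analysis.

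The case of 45 analysed is the pessimistic edge. Dropout is expected below 25%, and HAM-D6 will be attempted in patients who drop out. That also stands.

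Four stronger readings are tempting, and the article does not support them:

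- **That baseline imbalance passes in full into the result.** Only (b − 1) times the imbalance does, with its sign reversed when b is below 1.
- **That the assumption checks make the reported test depend on the data.** The text says that they will be made, but states no switching rule and no alternative test.
- **That randomisation is known to be unstratified by severity.** The article describes blocks and is silent on strata.
- **That the Table 3 wording, "The primary endpoint is the mean difference in scores between treatments at baseline and day 42", defines a rival endpoint.** The abstract and the statistical section both state change from baseline. The Table 3 line reads as loose shorthand, and it does not bear on the choice between t-test and ANCOVA.

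**Conclusion.** The point holds as an improvement in efficiency, not as an error of validity. The article fixes a primary test that makes only restricted use of a baseline value that is collected anyway.

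The direction is firm: apart from the one degree of freedom, ANCOVA is not less precise in large samples. The size is not firm. Over the assumed range the variance falls by 15% to 35% with equal SDs, and by 0% to 15% if the baseline SD is 0.7 of the day-42 SD. The main power figures rest further on reading 3.5 as the SD of change. A reader might infer that adjustment will make good the power lost to dropout. It may do so (90.0% with 45 analysed at k = 1, r = 0.5), but it may also recover nothing (80.2% at k = 0.7, r = 0.7).

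**What to change.** Before unblinding, define the primary analysis as the treatment difference in day-42 HAM-D6 adjusted for baseline HAM-D6, with a 95% confidence interval. This can be ANCOVA, or the day-42 contrast of the planned mixed model with baseline as a covariate; name one of the two. Keep the t-test on change, in Welch form, as a sensitivity analysis. State also whether 3.5 is the SD of the change or of the score.

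The cost is a change of wording and one degree of freedom. No further patients, visits or data are needed.
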